### Sample size and power calculation

Assuming that the source analyses are focused on transmission to the index children, and after accounting for the anticipated accrual goal and drop-out rate, a total of 1500 samples from 100 children (13 non-diarrheal and 2 diarrheal stools per index child on average from recent HDSS data) will be included in the analysis. We assumed a design effect of 1.7 to account for correlation between samples from same child, based on the intraclass correlation coefficient of (ICC) 0.05 for *Shigella* and *Campylobacter* detections within samples from the same child in the MAL-ED study^[2]^. We assume the design effect will be similar across *Shigella* and individual *Campylobacter* species. Assuming that 10% of each type of environmental sample tests positive for the target pathogen and the overall prevalence of pathogen infection is 20%, we would have 80% power to detect a risk ratio of 1.76 for each pathogen species and environmental pathway in a two-sided test with alpha=0.05. The minimum detectable risk ratio at 80% power varies by the proportion of environmental samples that test positive for the pathogen and by alternative assumptions for the design effect (Figure 1). Over a range of plausible design effects and pathogen prevalence in varied environmental sample types, we will have power to detect risk ratios that will identify the most important transmission pathways for *Shigella* and the most prevalent individual *Campylobacter* species.

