### Data analysis

The goals of the analysis are to identify possible sources and transmission pathways for *Shigella* and *Campylobacter* using two complementary approaches of statistical and mathematical modeling, whereby the former helps inform the latter. Specifically, we will generate measures of disease incidence, pathway-specific relative risks, environmental contact rates, and duration of pathogen shedding, all of which will inform and parameterize the transmission models. We will then develop complementary transmission models to characterize the relative importance of person-to-person and environmental transmission.

To identify potential sources for infections in index children, we will compare the prevalence of the target pathogen in environmental and familial samples between infected and uninfected index children. We will evaluate possible sources for *Shigella* as well as for *Campylobacter* species identified in at least 5% of stool samples from index children. Source types will be categorized into six pathways with their respective sample types: people (samples: caregiver and sibling stools), animals (animal feces), flies, food, water, and soil. Pathogen burden in each pathway will be characterized as the total qPCR Cq-derived quantity of species-specific pathogen detected in samples from that pathway. The duration of convalescent shedding will be estimated based on the median time from the onset of symptoms to the final positive convalescent stool performed on all qPCR-positive convalescent stool samples.

We will estimate the associations between pathogen quantity in an environmental pathway and infection in the index child using log-binomial regression with generalized estimating equations to account for correlation between samples from the same child over time. We will adjust for age and month of the year given the expected seasonality of exposure. Using the estimated relative risks for each transmission pathway, we will estimate attributable fractions (AF), where AF = 1 – 1/RR and RR is the relative risk for each pathway. We have previously used the attributable fraction methodology to attribute diarrhea etiologies^[18,27]^, a metric that accounts for both the prevalence of detection in a given pathway as well as the strength of association with infection and will provide a rank ordering of the relative importance of each pathway. The estimated relative risks will be used in the transmission models as described below.

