The goal of the infection transmission modeling is to understand where the transmission of different enteric pathogens falls on the continuum from primarily person-to-person to primarily environment-to-person transmission, using *Shigella* and *Campylobacter* as model organisms. Our infectious disease transmission modeling approach will consist of two complementary frameworks. First, we will develop an individually based household dynamic transmission model to capture the PCR-confirmed incidence of clinical and subclinical *Shigella* and *Campylobacter* infections observed in this study. Prevalence and duration of shedding in convalescent stools will help to parameterize two model parameters: shedding rate and a factor converting shedding from humans into increases in environmental contamination. Second, we will use a compartmental model framework to develop an endemic transmission model of the cohort. We will incorporate the prevalence of collected household characteristics, environmental contacts and measured environmental exposures (water, food, flies, etc.). Finally, relative risks estimated from the associations between detections in environmental and familial samples and infections in the index child will provide informative priors for parameters that characterize the importance of person-to-person and environmental transmission.

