## Figures and Tables

**Figure 1. F1:**
[figure not shown]
Power calculation for associations between detection of pathogens in the environment and children based on varied assumptions about the design effect and proportion of environmental samples that are positive.

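### The pathway relative risks are estimated for pathogen quantity, with no stated contrast, but are powered and passed to the transmission models as relative risks for detection

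*Protocol article*

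**What the plan says.** The protocol article uses two exposures for what it treats as one set of RRs.

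**Detection.**
- Sample size and power calculation: "Assuming that 10% of each type of environmental sample tests positive for the target pathogen", with 20% overall prevalence of infection, gives 80% power for an RR of 1.76, claimed for each pathogen species and each environmental pathway.
- Figure 1 (power) caption: "associations between detection of pathogens in the environment and children".
- Data analysis, transmission-modelling paragraph: the informative priors come from "relative risks estimated from the associations between detections in environmental and familial samples and infections in the index child".
- The Abstract also describes the association analysis in terms of detection. The source analysis opens with a comparison of pathogen prevalence in environmental and family samples between infected and uninfected index children.

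**Quantity.**
- Data analysis: the burden in each of six pathways is the total Cq-derived quantity over that pathway's samples. The only regression described is this one: "We will estimate the associations between pathogen quantity in an environmental pathway and infection in the index child". Its RRs go into AF = 1 - 1/RR, the AFs rank the pathways, and the same RRs are said to be used in the transmission models.

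The article states no unit, reference level or contrast for quantity, and describes no regression on detection.

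**The concern.** A quantity coefficient and a detection coefficient answer different questions on different scales. The first is a change in risk per unit of pathogen load; the second compares any pathogen with none. The article estimates the first and then describes it as the second when it reaches the priors.

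Three products depend on this RR. The AF and the rank ordering of pathways serve the primary objective of identifying sources and routes. The informative priors steer the person-to-person versus environmental split in the transmission models. The power statement is the study's justification of size. If the RR is entered per unit of quantity, the AF and the ranking follow the unit chosen, and the priors are set for an exposure other than the one the modelling paragraph names.

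**Working it through.** **1. What the 1.76 is.** Inputs from Sample size and power calculation: "a total of 1500 samples from 100 children (13 non-diarrheal and 2 diarrheal stools per index child on average"; "We assumed a design effect of 1.7 to account for correlation between samples from same child", which agrees with the "intraclass correlation coefficient of (ICC) 0.05" since 1 + 14 × 0.05 = 1.7; 10% of environmental samples positive; 20% overall prevalence; two-sided alpha 0.05.

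Effective N = 1500/1.7 = 882, or 88 exposed and 794 unexposed. Overall prevalence of 20% gives p0 = 0.20/(0.9 + 0.1 × RR). At RR 1.76, p0 = 0.186 and p1 = 0.327.

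| Two-proportion formula | Power at RR 1.76 | Detectable RR at 80% power |
|---|---|---|
| Pooled variance | 0.848 | 1.70 |
| Pooled, continuity-corrected | 0.818 | 1.74 |
| Unpooled variance | 0.778 | 1.79 |

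Using only the 1,300 non-diarrheal stools (N = 765), the pooled formula gives 1.76 at power 0.80. The figure is therefore recovered, approximately or closely, as an RR for detected versus not detected.

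**2. Detectable RR on a quantity scale.** The article gives no distribution for quantity, so this step rests on assumptions: log10 quantity is zero for negatives, 10% are positive, and a log-binomial Wald approximation holds. The detectable log RR per SD is (1.96 + 0.842)/√(882 × 0.20/0.80) = 0.189, an RR of 1.21 per SD. For positives with mean m and standard deviation s, the SD of the exposure is √(0.1(s² + m²) - (0.1m)²).

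| Positives: mean, SD (log10) | RR per log10 | RR at mean positive vs none | AF per log10 | AF at mean positive vs none |
|---|---|---|---|---|
| 2, 1 | 1.32 | 1.74 | 0.24 | 0.43 |
| 3, 1 | 1.22 | 1.81 | 0.18 | 0.45 |
| 4, 1 | 1.16 | 1.84 | 0.14 | 0.46 |
| 4, 1.5 | 1.16 | 1.79 | 0.14 | 0.44 |

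The same approximation for binary detection gives 1.88. The detectable RR thus has no single value until the unit is fixed. At a whole-exposure contrast (mean positive versus none), the AF is close to the detection value, 1 - 1/1.76 = 0.43.

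**3. Dependence of the AF on the unit.** For an RR of 1.2 per log10, AF = 1 - 1/1.2 = 0.17 over one log10 and 1 - 1/1.2³ = 0.42 over three. The fitted line is the same in both cases.

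**4. Ranking.** Illustration with assumed values. Pathway A has a detection RR of 1.76 and positives averaging 2 log10 above negatives. Pathway B has a detection RR of 2.0 and positives averaging 4 log10.
- By detection: A 1 - 1/1.76 = 0.43, B 1 - 1/2.0 = 0.50. B ranks first.
- Per log10: A 1 - 1/1.76^(1/2) = 0.25, B 1 - 1/2.0^(1/4) = 0.16. A ranks first.

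**5. Power under the mismatch.** Simulation with 1,500 runs, N = 882, 10% positive, positives with mean 3 and SD 1 log10, and robust Poisson regression in place of the log-binomial GEE.

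| True effect | Detection regressor | Quantity regressor |
|---|---|---|
| Detection, RR 1.76 | 0.87 | 0.84 |
| Log-linear in quantity, RR 1.76 at the mean positive | 0.88 | 0.91 |

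**6. Sample type versus pathway.** The 10% is stated per sample type, and the RR of 1.76 per pathway. Assuming independent types at 10% each, two food types (milk, porridge) give 1 - 0.9² = 19% and five animal types give 1 - 0.9⁵ = 41%. With N = 882, the detectable RR for detection (pooled to unpooled variance) is 1.70-1.79 at 10%, 1.55-1.59 at 19% and 1.46-1.47 at 41%.

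**The case against.** Much of the case on the other side stands.

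- A reader might infer that AF = 1 - 1/RR does not apply to a quantity exposure. That is wrong: the formula holds for any defined contrast, including observed quantity versus none. What is absent is the contrast. A condensed article may leave the unit to the full protocol or SAP, but no added unit would make both the regression sentence and the priors sentence true of one RR.
- A reader might infer that AFs would shrink, say from 43% to 13% if an RR of 1.76 spans 4 log10 (1.76^(1/4) = 1.15). That drop comes from choosing a one-log10 contrast, which the article never specifies. At the mean positive quantity versus none, the AF stays at 0.43 to 0.46.
- A reader might infer that the study is underpowered. The simulation does not support this.
- The 1.76 is not unrelated to the planned analysis, because the source analysis includes a prevalence comparison to which a binary calculation applies. That comparison is not, however, described as the source of the RRs for the AF or the priors.
- The article makes 1.76 conditional on 10% positivity and says that it varies with positivity, referring to Figure 1. Pooling lowers the detectable RR, so 1.76 is conservative for pooled pathways. The 19% and 41% also assume a full set of samples, whereas the article collects up to five animal types and takes milk and porridge only when available.
- Replacing quantity by detection is not the only sound repair, and any-versus-none can saturate. If each of five animal types were 30% positive and independent, 1 - 0.7⁵ = 83% of visits would count as exposed.

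**Conclusion.** The contradiction is in the current text and should be resolved: the same pathway RRs are estimated for quantity and described as detection RRs where they become priors. The power statement and its figure also use detection. The consequence is for meaning and scale. The AF and the pathway ranking are undefined until a contrast is fixed, and the ranking can reverse between a detection contrast and a per-log10 contrast. The 1.76 is a detected-versus-not-detected RR at 10% positivity and cannot be read as the detectable RR for a quantity coefficient.

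The documents do not support a claim that the AF formula is invalid, that the AFs would be wrong by a given amount, or that material power is lost. The mismatch itself rests on the text alone. The per-log10 values, the reversal example and the simulated powers rest on assumed quantity distributions, and the pooled-pathway figures on independent sample types at 10% each.

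**What to change.** Use one exposed-versus-unexposed contrast for the AF, the ranking and the priors. Either route reconciles the text:

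1. Fit the same GEE with detection of the same species in the pathway (any positive versus none) and take the RRs for the AF, the ranking and the priors from that model. Report log10 quantity alongside as a dose-response model.
2. Keep quantity as the exposure, state its scale, and compute the RR and AF at the observed quantity versus none detected. Reword the power section, the Figure 1 caption and the priors sentence to match.

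The first needs less rewording, because the power section, the figure and the priors already speak of detection. The second keeps the dose information in the main model and avoids saturation in pooled pathways.

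In either case, state that 1.76 is a detected-versus-not-detected RR at 10% positivity. Add that pathways pooling several sample types would have higher positivity and a smaller detectable RR, about 1.55-1.59 at 19% and 1.46-1.47 at 41% under the independence assumption.

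The cost is one extra model per pathway, a short recalculation and some rewording. No new data are needed.

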### Characterization of the home environment

At the baseline visit, a semi-structured questionnaire will be used to assess participant sociodemographic characteristics as well as characteristics of the household environment, such as water and sanitation access, house construction materials, presence of handwashing equipment, animal ownership and housing conditions, and food storage and preparation materials at the baseline home visit.

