### Monthly household visits and spot checks

During each monthly visit to collect environmental samples, we will conduct a brief household survey and spot-check to record water, sanitation, and hygiene behaviors and indicators of child exposure. Questions include the frequency of observed child ingestion of soil, child mobility, child breastfeeding and feeding practices, animal ownership, animal confinement, animal feces management, frequency and cleaning of animal-raising locations. Spot check observations will include the presence of water storage containers, handwashing stations, soap at handwashing stations, feces on the floor of the latrine, food storage practices, and animals in living spaces, and animal confinement structures.

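### Pathway relative risks are adjusted for age and month only, so shared household conditions can give an inert pathway a relative risk above 1; the size cannot be found from the protocol

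*Protocol article*

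**What the plan says.** The Data analysis section of the protocol article relates pathogen quantity in each pathway to infection in the index child by "log-binomial regression with generalized estimating equations to account for correlation between samples from the same child over time". The next sentence gives the covariates: "We will adjust for age and month of the year given the expected seasonality of exposure". No other covariate is named there or elsewhere for this regression.

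The RRs have two later uses. First, "we will estimate attributable fractions (AF), where AF = 1 – 1/RR and RR is the relative risk for each pathway", and these fractions rank the pathways. Second, in the transmission-modelling paragraph the RRs supply informative priors for the importance of person-to-person and environmental transmission.

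The study collects much of what would describe the household. The baseline questionnaire covers sociodemographic data and "characteristics of the household environment, such as water and sanitation access, house construction materials, presence of handwashing equipment, animal ownership". The monthly visits are to "record water, sanitation, and hygiene behaviors and indicators of child exposure", with questions on "child breastfeeding and feeding practices, animal ownership, animal confinement, animal feces management". The only analytic use stated for the household characteristics is that their prevalence enters the compartmental model.

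**The concern.** Contamination of a household's water, food, soil and flies is not assigned at random. Poor sanitation, crowding or poverty can raise contamination of several pathways and also raise the child's infection risk by other routes. An RR adjusted for age and month takes up part of that shared cause. Age and month do not stand in for it: households of very different condition are enrolled at the same child age and in the same season.

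GEE does not solve this. It allows for correlation between samples from one child, so that the standard errors are right. It does not remove bias from a cause that differs between households. Nor does using household characteristics in the compartmental model, since the RRs have been estimated by then.

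At stake is the primary objective, identifying likely sources so that interventions can be aimed at them. An inert pathway with an RR above 1 gets a positive attributable fraction and a place in the ranking, and passes the same error on as a prior.

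**Working it through.** **Inputs from the sample-size section:** 1500 samples from 100 children (15 each), intraclass correlation (ICC) 0.05, design effect 1.7, 10% of environmental samples positive, 20% infection prevalence, 80% power at RR 1.76, two-sided alpha 0.05. As in that section, exposure is treated here as positive or negative, although the regression uses quantity.

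**1. The plan's own figure.**
- Design effect = 1 + (15 − 1) × 0.05 = 1.70, as stated.
- Effective n = 1500/1.7 = 882.4, that is 88.2 exposed and 794.1 unexposed.
- At RR 1.76 with 20% overall, the unexposed risk is 0.20/(0.9 + 0.1 × 1.76) = 0.186 and the exposed risk 0.327.
- Power is 81.8% with a continuity-corrected two-proportion test, 84.8% without the correction and 77.8% with unpooled variance. The stated 80% is reproduced. It takes the RR as unconfounded.

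**2. Crude upper range for an inert pathway (true RR 1).** Assumption: all between-child variation is a household trait, present in half the homes.
- Between-child SD of risk = √(0.05 × 0.2 × 0.8) = 0.0894, so the two halves have risks 0.1106 and 0.2894.
- Assumed positivity 5% in the low-risk half and 15% in the high-risk half (mean 10%):
  - exposed risk = (0.05 × 0.1106 + 0.15 × 0.2894)/0.20 = 0.2447
  - unexposed risk = (0.95 × 0.1106 + 0.85 × 0.2894)/1.80 = 0.1950
  - RR = 1.25, attributable fraction = 1 − 1/1.25 = 20%
- Assumed positivity 2% and 18%: 0.2716/0.1920, RR = 1.41, attributable fraction 29%.

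**3. The same settings through GEE.** Simulation with 100 children × 15 samples, log link and exchangeable working correlation:

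| Share of between-child variance at household level | 5%/15% | 2%/18% |
|---|---|---|
| All | about 1.15 | about 1.24 |
| Half | about 1.07 | about 1.14 |

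A repeat with other random numbers gave 1.14, 1.23, 1.09 and 1.14. The plan does not state the working correlation. With independence and all the variance at household level, the repeat gave 1.22 and 1.42, close to the crude values.

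**4. Does adjustment remove it?** Further simulation, inert pathway, half the households with a trait that multiplies positivity by a and infection risk by b (assumed values, 400 runs each). Ranges run over exchangeable and independence correlation:

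| a, b | RR without the trait | False-positive rate without the trait |
|---|---|---|
| 2, 2 | 1.08–1.10 | 11–12% |
| 3, 2 | 1.13–1.19 | 13–25% |
| 3, 3 | 1.12–1.28 | 13–40% |

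With the trait in the model, RR is 0.98–1.00 and the false-positive rate about 4–8%.

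**5. A weak confounder.** RR_obs = [1 + q1(RR_U − 1)]/[1 + q0(RR_U − 1)], where RR_U is the confounder's own RR and q1, q0 its prevalence with and without exposure. For RR_U = 1.5, q1 = 0.6, q0 = 0.4: 1.3/1.2 = 1.08, attributable fraction 8%, chance of significance 6%. This is hardly distinguishable from no bias.

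**The case against.** **The covariate list may not be complete.** The sentence gives one reason, seasonality, and does not say that nothing else will be added. The document is a condensed article, and a fuller plan may hold more. This stands against any reading that the study has decided not to use its household data. It does not remove the point: the article fixes a named set for its main regression, and nothing in it adds to that set.

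**The magnitudes are assumed.** This stands. The 5%/15% and 2%/18% contrasts are not in the documents and are aligned fully with the risk halves. The ICC also contains prolonged shedding, so only part of it is household-level. The crude table overstates what exchangeable GEE would give.

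**A reader might infer that the bias could reach the plan's detectable RR of 1.76.** The formula in step 5 gives 2.6/1.4 = 1.86 for RR_U = 3, q1 = 0.8, q0 = 0.2. As a fixed household trait this does not fit the plan's figures. Its overall prevalence would be 0.1 × 0.8 + 0.9 × 0.2 = 0.26. The risks would be 0.20/1.52 = 0.132 and 0.395, and the between-child variance 0.26 × 0.74 × 0.263² = 0.0133. That implies an ICC of 0.0133/0.16 = 0.083, above the 0.05 assumed.

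**A reader might also infer that attributable fractions adding up to more than 100% would show the confounding.** They would not. With 1 − 1/RR for each of six pathways, unconfounded RRs can also exceed 100% in total. That follows from the formula, and covariates do not change it.

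**The aim is exploratory.** The objective speaks of potential sources, to be confirmed by later interventions. This limits the harm but does not remove it, because the ranking decides which pathways go forward.

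**Adding every covariate would be wrong.** This stands and shapes the fix. Soil is not collected in homes with cement floors, and milk and porridge only if available that day, so floor type and feeding partly decide whether the exposure exists.

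**Conclusion.** The concern holds as a possibility that the plan as written leaves open, not as a demonstrated bias. With age and month as the named covariates, a pathway with no effect can show an RR above 1 and carry it into the ranking and the priors. Under assumed confounders that RR runs from about 1.07 (weak confounding, or exchangeable GEE with half the between-child variance at household level) to about 1.25–1.4. The upper range takes all of the ICC of 0.05 as household-level, the assumed 5%/15% or 2%/18% contrasts, and a crude table.

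The documents do not support a claim that the RRs will be biased by a given amount, or that the order of the pathways will change. A shared cause may lift several pathways together, and no calculation here shows a change in rank. The change is still worth making: the data are collected, the RRs feed two later analyses, and source identification is the primary objective.

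**What to change.** 1. **Adjusted RR model, pathway by pathway.** Beside age and month, prespecify already collected household confounders, for example sociodemographic status, household size, water and sanitation access, housing and breastfeeding status. Choose them from a causal diagram for each pathway. Leave out variables that lie on the causal path of the pathway under study or that decide whether it is sampled, such as floor type in the soil model, or feeding status where it determines whether food is sampled.
2. **Within/between-child split beside it.** Enter exposure as the child's mean and the deviation from that mean. The deviation term is free of fixed household confounding without any choice of covariates. It is not free of time-varying confounding.
3. **Downstream use.** State that the attributable fractions and the priors use the adjusted RRs.
4. **Joint six-pathway model as secondary only.** Some pathways are structurally unsampled in some homes or on some days, so the joint model would rest on a selected subset.

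Cost: analysis wording and no new data. Intervals will be wider, a few degrees of freedom are spent with 100 clusters, and the within-child term loses precision where exposure varies little over time.

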## METHODS

### Study setting

The study participants will be recruited from four villages surrounding Haydom, Tanzania. The study area has been extensively described^[10,17]^. In brief, Haydom is characterized by poor road infrastructure in a highland setting and primarily dependent on subsistence agriculture and livestock keeping. The area has a high rate of childhood malnutrition and bacterial carriage, previously linked with poor linear growth^[10]^. Understanding how children and the entire household are exposed to these pathogens through the environment is critical for designing targeted and context-specific interventions. The research team has substantial experience with community recruitment, performance of longitudinal cohort studies, sample collection and processing, and the use of molecular methods for detection of enteric pathogens ^[17,18]^.

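### Pathway relative risks adjusted only for age and month can carry stable household confounding into the AF ranking and the transmission-model priors; adjust for recorded household traits and show a within-household RR beside the pooled one

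*Protocol article*

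**What the plan says.** The Data analysis section sets out the source comparison: "we will compare the prevalence of the target pathogen in environmental and familial samples between infected and uninfected index children". The model is fitted "using log-binomial regression with generalized estimating equations to account for correlation between samples from the same child over time", and its adjustment set is given in one sentence: "We will adjust for age and month of the year given the expected seasonality of exposure".

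The resulting RRs are used twice. They are converted to AF = 1 - 1/RR, which "will provide a rank ordering of the relative importance of each pathway". They also "will provide informative priors for parameters that characterize the importance of person-to-person and environmental transmission".

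Household traits are recorded. The baseline questionnaire will "assess participant sociodemographic characteristics as well as characteristics of the household environment" (Characterization of the home environment), and the monthly visits add spot checks. The only analytic use stated for household characteristics is the compartmental transmission model. On village, Study setting says: "The study participants will be recruited from four villages surrounding Haydom, Tanzania". No analytic use of village is stated.

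**The concern.** Each home contributes about 15 index-child stools over a year, so a pooled RR mixes two contrasts. One compares homes that are generally more contaminated with homes that are generally less so. The other compares months when a given home is contaminated with months when it is not. Any stable trait that raises both contamination and infant infection confounds the first contrast.

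Age and month are poor stand-ins for such traits, because enrollment is balanced over age and season and every home is followed for 12 months. GEE deals with the variance, not the bias. Putting all pathways into one model would not cure it either, since wealth, sanitation and village are not sampled pathways.

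These RRs are the source analysis for the primary objective. A pathway that partly marks poorer homes could move up the ranking, and the priors would take the same bias into the estimates of person-to-person and environmental transmission.

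**Working it through.** **Inputs from the protocol (Sample size and power calculation).** 100 children, 1500 stools (15 each), infection prevalence 0.20, exposure prevalence 0.10, and a design effect "based on the intraclass correlation coefficient of (ICC) 0.05".

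**The plan's own figure.**
- Design effect = 1 + (15 - 1) x 0.05 = 1.70. Effective N = 1500/1.7 = 882 (88 exposed, 794 unexposed).
- At RR 1.76, p0 = 0.2/(0.9 + 0.1 x 1.76) = 0.186 and p1 = 0.327.
- A continuity-corrected two-proportion test has 81.8% power. Minimum detectable RRs under common formulas run from 1.64 to 1.79.
- The stated RR of 1.76 at 80% power is therefore reproduced within the spread of methods.

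**What the ICC implies.** An ICC of 0.05 at 20% prevalence means that infection risk differs between children with SD = sqrt(0.05 x 0.20 x 0.80) = 0.089, or 8.9 percentage points. The plan thus already assumes stable differences between children. What it does not give is how far these go with contamination.

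**Assumed inputs.** The exposure ICC, and the correlation r between a home's contamination propensity and its infection propensity.

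**Closed form for a pathway with no effect.** Let cov = r x sqrt(exposure ICC x 0.10 x 0.90) x 0.0894. Then P(infected | exposed) = 0.2 + cov/0.1, P(infected | unexposed) = 0.2 - cov/0.9, and the spurious RR is their ratio. Example with r = 0.5 and exposure ICC 0.10: cov = 0.5 x 0.0949 x 0.0894 = 0.00424, so RR = 0.2424/0.1953 = 1.24.

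The simulations used 100 homes x 15 samples, beta-distributed home propensities linked by a Gaussian copula, a log-link fit with working independence and cluster-robust SE, and a true RR of 1.

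| r | Exposure ICC | cov | Closed-form RR | Simulated pooled RR | False positives (nominal 5%) |
|---|---|---|---|---|---|
| 0.1 | 0.10 | 0.00085 | 1.05 | 1.05 | 6% |
| 0.2 | 0.10 | 0.00170 | 1.10 | 1.08-1.09 | 10-12% |
| 0.5 | 0.05 | 0.00300 | 1.17 | 1.15-1.16 | 17-18% |
| 0.5 | 0.10 | 0.00424 | 1.24 | 1.22-1.24 | 27-31% |
| 0.5 | 0.20 | 0.00600 | 1.34 | 1.31 | 41% |
| 0.5 | 0.30 | 0.00735 | 1.43 | 1.37 | 53% |

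The closed form runs slightly high because a copula correlation r gives a somewhat lower correlation between the probabilities themselves. At r = 0 and exposure ICC 0.05-0.2 the pooled test rejects 5.4-5.9% of the time, so the inflation comes from r. The within-household RR in these settings was 0.99-1.01, with 4-7% false positives.

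**The same point without a copula.** Suppose a trait is present in half of homes and doubles both exposure and infection. Exposure is then 0.067 or 0.133, and infection 0.133 or 0.267.
- P(infected | exposed) = (0.067 x 0.133 + 0.133 x 0.267)/0.2 = 0.222.
- P(infected | unexposed) = (0.933 x 0.133 + 0.867 x 0.267)/1.8 = 0.198.
- RR is about 1.13 and AF = 11%.

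Tripling exposure and doubling infection gives RR 1.19 (AF 16%). Tripling both gives 1.29 (AF 22%), with an implied infection ICC of 0.01/0.16 = 0.063, slightly above the plan's 0.05.

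**Effect on the ranking.** A null pathway with spurious RR 1.22 has AF = 1 - 1/1.22 = 18%. A genuine source with RR 1.15 has AF = 1 - 1/1.15 = 13% and would rank below it.

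**What a covariate can do.** At r = 0.5 and exposure ICC 0.10, a household covariate that captures 80% of the shared factor cut the spurious RR from 1.23 to 1.03 and false positives from 28% to 6%.

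**Limits.** Exposure was binary, as in the power calculation. The plan models quantity, to which the same argument applies.

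**The case against.** The other side has real strength.

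- **The key input is assumed.** The document gives neither r nor an exposure ICC. At r = 0.1 the bias is about 5%, with false positives close to nominal. All the spurious RRs in the table lie below the design RR of 1.76. This stands, and it limits the claim to one of possible bias.
- **The article is cautious and condensed.** It speaks of possible sources and associations, leaves confirmation to later interventions, and brings household characteristics into the compartmental model. A fuller covariate list may exist elsewhere. Yet the article does not leave adjustment open: it names a set and gives the reason. The compartmental model is not the regression that yields the RRs.
- **The within-household contrast has its own faults.** With a true RR of 1.76, no confounding and an assumed 50% chance of detecting contamination, pooled and within-household RRs were 1.65 and 1.47-1.51 at exposure ICC 0.3. At ICC 0.5 they were 1.60 and 1.34-1.35, with power 85-89% and 43-47%. Pathways that persist in a home would be marked down. Nor does the contrast deal with reverse contamination: if an infected child raises same-visit contamination 1.5-fold (assumed) and there is no true effect, pooled RR is 1.35 and within-household RR 1.39, each with 52% false positives. This stands in full.
- **Adjusting every model for everything goes too far.** Animal ownership governs whether animal feces can be sampled, and homes with cement floors give no soil sample. Conditioning on such variables in their own pathway removes much of the exposure contrast. This stands.

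A reader might infer that harmless pathways will be named as sources, or that the within-household RR should replace the pooled one. The document supports neither. The first needs a value of r that it does not give; the second would exchange one ranking distortion for another.

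**Conclusion.** The point holds as a worthwhile, cheap improvement to the primary source analysis. With only age and month in the model, stable differences between homes can bias the pooled RRs, and the AF ranking and priors inherit that bias. GEE does not prevent it.

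With infection ICC 0.05 and exposure ICC 0.05-0.2, a pathway with no effect would show an RR of about 1.05-1.1 at r = 0.1-0.2. At r = 0.5 it would show about 1.15-1.3, with 17-41% false positives. Larger figures (RR up to 1.52, false positives up to 76%) need r = 0.8 and an exposure ICC of 0.2, and should not be read as expected. If contamination and infection risk were negatively correlated across homes, the bias would run the other way and could hide a true source. Because the ranking rests on point estimates, even moderate bias can change the order of pathways.

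**What to change.** In Data analysis:

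1. Add village and the baseline socioeconomic and sanitation variables to each pathway model. Leave out those that define that pathway's own exposure: animal ownership in the animal model, water access in the water model, floor or house material in the soil model.
2. Split each pathway exposure into the household's mean over its visits and the visit's deviation from that mean. Report the within-household RR (the deviation term) beside the adjusted pooled RR. Show the AF ranking and the priors under both, and flag any pathway whose rank changes.
3. State the limits of the within-household RR. It loses power and is attenuated more by imperfect detection where contamination persists in a home. It does not remove time-varying confounding or contamination of the home by the infected child.

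A comparison of mismatched *Campylobacter* species (one in the home, another in the child) can be added as a supportive check at most, since species may share sources.

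The cost is analysis wording and analyst time; no new data are needed. With perfect detection, within-household power at RR 1.76 was 94-96% at exposure ICC 0.1 (pooled 95-97%), 93% at 0.2 (pooled 94-95%) and 79% at 0.5 (pooled 87%). Only homes with varying exposure and at least one infection inform this contrast: about 56-65% of homes at exposure ICC 0.05-0.10 and 37-39% at 0.30.
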